#### Data analysis

This being a feasibility study, descriptive findings concerning recruitment numbers, completions, drop-outs, and summary estimates of outcome measures at baseline and follow-up focussing on the dropout rate at each time point will be explored. We will also conduct exploratory analyses of the pre-post effect of the intervention using the data from participants who have completed the programme. To examine differences before and after using MePlusMe, we will conduct a 4 × 4 repeated measures ANOVA with time (four time-points) and the four assessments (PHQ-9, GAD-7, Edinburgh-Warwick Mental Wellbeing scale, Academic Self-Efficacy scale, and VAS ratings) as the within-subject variables. Effect sizes will be presented as Cohen’s *d.* This will enable determination of the outcome measure mean, standard deviation and variance, and change, which will be essential for designing an appropriately powered trial.

Qualitative data from the feedback form will be analysed using content analysis. Interviews and analyses will be performed concurrently using the principles of constant comparison [42] and thematic analysis [43]. At least two researchers will independently code the first interview and agree on descriptive codes. These codes, and where appropriate further new codes, will be applied to subsequent transcripts. Consistency in coding will be checked within the research team. Descriptive codes will be collated into themes and a preliminary explanatory framework devised. This will be used as the basis for coding and for informing future interviews. The robustness of themes will be tested by examining differences and similarities between coded data.

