### Intervention

Following screening, students will decide whether they want to access the Library, directly choosing the techniques they are interested in or whether they want guided help, entering the Questionnaire route to identify their difficulties. Should they choose the Questionnaire route, the students will be presented with the initial screen of the system which poses the question ‘What is your hotspot today?’ allowing each student to come into the questionnaire with whatever they think the presenting problem is. The three entry points are (i) ‘It’s how I am feeling inside’, addressing psychological difficulties, (ii) ‘It’s my studies’, addressing study skills problems, and (iii) ‘It’s outside pressures’. However, the questionnaire is designed in such a way that no matter which entry point the student chooses, they will always be directed to the other points at the end of each section.

Once they choose the techniques they are interested in from the Library or upon completion of the Questionnaire, the student will be asked to rate how much their difficulties are currently affecting their life. They will then have the opportunity to name their package of techniques so that they can later find it in their personal space. At this stage, they will also decide whether they want reminders to encourage them to return to watch the videos and practice the techniques. They will then be guided to My Place where they will have access to the package with the techniques. The student will be asked to rate again at different intervals (2, 4, and 8 weeks from baseline) how much their difficulties are affecting their life after practising these techniques, and their responses will result in a graph indicating their progress over time as a self-monitoring tool. If the students give two consecutive low ratings, they will be prompted by email with information on where to seek further support. Moreover, it is stated in the description of some techniques (e.g. the two psychoeducation techniques of understanding stress and understanding low mood) that if symptoms persist for more than 2 weeks, then students should seek support elsewhere (specific referrals are again provided). Students can make notes of their thoughts regarding the techniques and their experience of them, and are given the option either to keep their thoughts private or to share them within the system’s built-in social network.

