#### Acceptability of intervention

A semi-structured interview will take place face-to-face with between 15 and 20 randomly selected participants who will have expressed an interest in providing qualitative information on their experience of using MePlusMe. For inclusion in the interviews, students will have to have used the system for two full months and completed all measurements. We will also recruit students who dropped out before the full 2 months to assess their reasons for doing so. The interview will last approximately 20 min, will be recorded with consent, and will be transcribed verbatim. It will explore a number of issues, such as the elements of the system that the participants liked or did not like (quality of implementation), the ways in which they felt that the system helped them or not, how often they used the system, whether they would have prefered to consult a counsellor or to have had access to alternative methods of support instead (fidelity), and what barriers might stop them from using the system in the future.

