### Assessments

Students will be asked to complete the measures of mood (symptoms of depression and anxiety), mental wellbeing, functioning, and study skills at baseline (T0) prior to using the intervention but after giving consent, and then again at 2 weeks (T1), 4 weeks (T2), and 8 weeks (T3) from baseline. The satisfaction feedback form will be sent to participants at week 4 (T2). By collecting information at this stage, we hope that the feedback will be more reliable as students will still be practising the techniques that we wish them to appraise. Finally, after 2 months, a semi-structured interview will take place with the subsample of participants (see Table 1).

**Table 1 Tab1:** Overview of outcome measures

		Time of measurement			
Instrument	Aim	T0 baseline (pre-testing)	T1 post-test (2 weeks)	T2 follow-up (4 weeks)	Τ3 follow-up (8 weeks)
PHQ-9	Symptoms of depression	x	x	x	x
GAD-7	Symptoms of anxiety	x	x	x	x
Edinburgh-Warwick Mental Wellbeing scale	Positive mental health (mental wellbeing)	x	x	x	x
Academic self-efficacy	Academic self-efficacy	x	x	x	x
VAS	Everyday functioning	x	x	x	x
Feedback form	Engagement and satisfaction of the end-users			x	
Interview (15–20 participants)	Qualitative assessment of the experience of using the system				x
Intervention delivery	Patterns of use of the system (e.g. duration of use, total number of visits)	x	x	x	x

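### The pre-post effect is estimated only in programme completers, which leaves dropouts' collected scores out of the effect analysis and may bias the change carried into the RCT's design

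*Protocol article*

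**What the plan says.** The Data analysis section plans two kinds of quantitative output.

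- **Descriptive.** Recruitment, completion and dropout counts are planned, and "summary estimates of outcome measures at baseline and follow-up focussing on the dropout rate at each time point will be explored". Nothing limits these summaries to completers.
- **Effect estimation.** "We will also conduct exploratory analyses of the pre-post effect of the intervention using the data from participants who have completed the programme". A repeated measures ANOVA over the four time points follows, with effects expressed as Cohen's d. No effect analysis of all participants is named. The section says the resulting means, SDs and change scores are ones "which will be essential for designing an appropriately powered trial".

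Under Assessments, the self-report measures are taken at baseline (T0) and "then again at 2 weeks (T1), 4 weeks (T2), and 8 weeks (T3) from baseline". The sample size section sets 186 evaluable participants and adds 56 for dropout, giving 242. It also says that testing clinical outcomes is not central to the design.

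Completing the programme is not defined for the analysis. Under Intervention, "students will decide whether they want to access the Library, directly choosing the techniques they are interested in" or follow a questionnaire to a suggested package. Under Acceptability of intervention, two months of use and completion of all measurements are listed as separate conditions for interview, and "We will also recruit students who dropped out before the full 2 months to assess their reasons for doing so".

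**The concern.** The article chooses an analysis set here; this is not a detail left for a fuller document. A student who leaves after week 2 or week 4 has already given two or three sets of scores, yet contributes nothing to the estimated change. The ANOVA in its usual form also drops a student who stays but misses one assessment.

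Membership of the set depends on what happens after baseline. If leaving is related to symptoms or to early change, the completers' mean change differs from that of everyone who started. An RCT would randomise everyone who starts, so a planning value taken from completers describes a different group.

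The Intervention section gives some reason to expect dropout related to outcome. Students who repeatedly give low ratings are emailed about other sources of support, and some technique descriptions point students elsewhere if symptoms persist. Because the programme is self-assembled, completion could mean use of the system, completion of the measures, or both, and each meaning gives a different set.

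**Working it through.** **1. The plan's dropout figure.** Inputs from the sample size section: 186 evaluable, 30% inflation.

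- 186 × 0.30 = 55.8, rounded to 56; 186 + 56 = 242. This reproduces the plan.
- Planned loss as a share of those recruited: 56 / 242 = 23.1%.

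This is a planning allowance, not an observed rate.

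**2. What is left out.** Assume that all 56 gave a baseline and that none has week 8 scores. Each then has one to three sets of scores (T0, perhaps T1, perhaps T2). That is between 56 and 56 × 3 = 168 sets per instrument left out of the effect analysis.

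**3. Bias by direct arithmetic.** Let q be the share lost and k the mean change in dropouts divided by that in completers. Change in all participants is (1 − q) + qk times the completer change, so completer/all = 1 / [(1 − q) + qk]. With q = 0.231:

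| k (assumed) | completer/all | completer change is |
|---|---|---|
| 0 | 1 / 0.769 = 1.30 | 30% too large |
| 0.5 | 1 / 0.884 = 1.13 | 13% too large |
| 1 | 1.00 | unbiased |
| 1.2 | 1 / 1.046 = 0.96 | 4% too small |

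The documents give no value for k.

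**4. Bias under an explicit dropout model.** All inputs are assumed: four visits, unit SD, correlation 0.6 between any two visits, and a true T0–T3 change of −0.40 SD (a fall is improvement). Dropout occurs after T1, with log-odds linear in the T0–T1 change, expressed in outcome SDs. Results from large simulated samples:

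| Loss | Who leaves (log-odds per SD) | Completer change | Against −0.40 |
|---|---|---|---|
| 23.1% | worsening, 1 | −0.48 | 20% too large |
| 23.1% | worsening, 0.5 | −0.45 | 11% too large |
| 23.1% | improving, 1 | −0.32 | 20% too small |
| 30% | worsening, 1 | −0.50 | 26% too large |
| 30% | improving, 1 | −0.30 | 26% too small |

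The 30% rows show sensitivity to a heavier loss than the plan allows for.

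Two details matter. In the first row, the completers' T3 mean equals the full-sample value (−0.40), and the excess change comes from a T0 mean about 0.08 SD higher. In this model the bias is therefore selection on baseline plus regression to the mean, not poor final scores removed from the data. The SD of change hardly moves (0.88 against 0.89), so the distortion is in the mean.

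**5. Possible effect on the later trial.** If the completer effect were carried over directly with the same SD, required N would vary as 1/d²:

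- 11% too large: 1 / 1.11² = 0.81 of the N needed.
- 20% too large: 1 / 1.20² = 0.69 of the N needed.
- 20% too small: 1 / 0.80² = 1.56 times the N needed.

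**The case against.** The strongest defence is that the study is primarily about feasibility, the analysis is labelled exploratory, and there is no control arm. Even an unbiased pre-post d is not the between-group effect an RCT needs, so completer selection is only one reason for caution in using it. This lowers the severity. It does not justify the restriction, because the same section names these estimates as inputs to the RCT's design.

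A reader might also infer more than the documents support:

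- *That completer change is necessarily inflated.* The documents contain no data on change in dropouts. Students may also leave because they feel better, and the sign then reverses. Interviewing dropouts about their reasons is an acceptability question and does not show that the plan regards dropout as informative.
- *That 30% of the sample is lost.* The 30% is applied to 186; as a share of 242 the allowance is 23%.
- *That dropouts' data are thrown away.* They can enter the descriptive summaries. What those summaries do not promise is an all-participant estimate of within-person change or Cohen's d.
- *That the analysis set is picked by outcome.* An undefined term is not evidence of that, and a precise definition may stand in a fuller document.

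A mixed model is not a complete cure either. It removes the bias under missing at random, but not if dropout depends on scores never observed.

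**Conclusion.** The point holds in a limited form. Restricting the effect analysis to completers leaves out scores already collected from an expected 56 of 242 participants (23%), if losses match the allowance. It also exposes the planning estimates to selection. Overstatement is plausible, but neither its presence nor its size is established. At 23% loss, the assumed dropout models in the working give a completer change 11% to 20% too large if worsening students leave and about 20% too small if improving students leave. If dropout is unrelated to symptoms and change, there is no bias, only lost information. The issue is of moderate severity, and its correction is a cheap improvement.

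**What to change.** In the Data analysis section:

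1. Make the main exploratory analysis a likelihood-based mixed model for each outcome. Include every consented participant with a baseline and all available T1–T3 scores, regardless of system use. Take the change estimates and Cohen's d from it.
2. State that this analysis is valid under missing at random.
3. Keep the completer analysis as a labelled secondary, and say whether completion means use of the system, completion of the measures, or both.
4. Report baseline scores of completers and non-completers side by side.

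The cost is analysis wording only, since the planned assessments already supply the data. The estimated effect may look less favourable than the completer figure.

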### Outcome measures

#### Mood and wellbeing

Upon submission of the consent form, students will complete validated clinical measures, namely the PHQ-9 [28], a widely used 9-item self-report measure of depression symptoms, and the GAD-7 [27], a 7-item scale commonly used in clinical and research practice to assess for current symptoms of anxiety and their severity. The Edinburgh-Warwick Mental Wellbeing scale will be used to assess positive mental health (mental wellbeing). This is a 14-item scale initially validated using student populations and additionally used in national survey studies.

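### The single 4 × 4 repeated measures ANOVA lists five instruments, and its omnibus tests pool unlike scales, so none of them tests change on any one outcome

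*Protocol article*

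**What the plan says.** Under Data analysis, the protocol article describes one model, of stated size 4 × 4, in which both factors are within-subject: a "repeated measures ANOVA with time (four time-points) and the four assessments (PHQ-9, GAD-7, Edinburgh-Warwick Mental Wellbeing scale, Academic Self-Efficacy scale, and VAS ratings"). The text counts four assessments, but the list names five instruments. Table 1 also shows five quantitative self-report instruments, each at all four visits. The visits are baseline and "then again at 2 weeks (T1), 4 weeks (T2), and 8 weeks (T3) from baseline".

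The Outcome measures sections describe the instruments:
- PHQ-9: "a widely used 9-item self-report measure of depression symptoms".
- GAD-7: "a 7-item scale commonly used in clinical and research practice to assess for current symptoms of anxiety and their severity".
- Wellbeing: "The Edinburgh-Warwick Mental Wellbeing scale will be used to assess positive mental health (mental wellbeing"), with 14 items.
- Academic self-efficacy: an adapted scale, score range not given.
- Everyday functioning: one 5-point Likert item, numeric coding not given. Table 1 and Data analysis call it a VAS.

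The Data analysis paragraph then says "Effect sizes will be presented as Cohen’s" d, and that the analysis will yield each measure's mean, SD, variance and change for designing the later trial. Earlier in the same paragraph it plans summary estimates of the outcomes at baseline and follow-up, and it labels the pre-post analysis exploratory.

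**The concern.** Two things look wrong. First, the stated dimensions contradict the list. Either the design is 4 × 5, or one unnamed instrument is to be left out.

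Second, making the instrument a within-subject factor treats raw scores on five unlike scales as repeated readings of one quantity. The study design section says the data will be used to judge candidate primary outcomes and to size the randomised trial. Both uses need results outcome by outcome. This ANOVA is the only inferential model described for the quantitative outcomes. A non-significant time effect could be read as no benefit, and a significant one as general benefit, when either may be an artefact of how the scales are scored.

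**Working it through.** **Step 1: dimensions.** There are 4 time points (T0 to T3). The instruments named are PHQ-9, GAD-7, wellbeing, academic self-efficacy and functioning, which makes 5. The design is 4 × 5, so the stated 4 × 4 does not reproduce.

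**Step 2: what each omnibus term measures on raw scores.**
- Time: change in the unweighted mean of the five raw scores. Units are mixed and the signs of improvement differ.
- Assessment: whether the mean raw scores of different questionnaires differ. This has no clinical meaning.
- Time × assessment: whether raw change differs between instruments. When scores do change, equal benefit still appears as unequal raw change, because the scales differ in spread and direction.

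**Step 3: cancellation, by arithmetic.** Let every instrument improve by d = 0.4 SD from T0 to T3. Take symptom scores and the functioning item as falling with improvement, and wellbeing and self-efficacy as rising. The change in the pooled mean is

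0.4 × (−SD_PHQ − SD_GAD + SD_wellbeing + SD_self-efficacy − SD_functioning) / 5.

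The document gives no SDs and no coding for the functioning item, so all of these are assumptions:

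| Assumed SDs (PHQ, GAD, wellbeing, self-efficacy, functioning) | Pooled change |
|---|---|
| 5, 5, 9, 10, 1 | 0.4 × 8/5 = +0.64 |
| 5, 5, 5, 6, 1 | 0.4 × 0/5 = 0 |
| 5, 5, 8, 1, 1 | 0.4 × (−2)/5 = −0.16 |

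The same standardised benefit gives a positive, zero or negative time effect.

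**Step 4: simulation.** Assumptions: N = 186 (the evaluable number in the sample size section), 0.4 SD improvement on every instrument by T3, within-person correlation 0.6, 500 runs, 5% level. The Monte Carlo standard error near 5% is √(0.05 × 0.95/500), about 1 percentage point.

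| Scenario | Time effect significant | Time × assessment significant |
|---|---|---|
| Four instruments, equal SDs, two falling and two rising | 4.8% | 100% |
| Five instruments, SDs 5, 5, 5, 6, 1 | 4.2% | 100% |
| Five instruments, SDs 5, 5, 9, 10, 1 | 79% | 100% |
| Five instruments, reverse-scored and standardised | about 100% | about 5% |

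The first three rows carry the same benefit on every instrument. The time effect ranges from the null rate to 79%, and the interaction is always significant although no instrument benefits more than another. Once the scales are aligned, both tests behave as intended.

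**Step 5: per-instrument contrast on the same data.** The standardised mean of the paired difference is 0.4/√(2 × (1 − 0.6)) = 0.447, and 0.447 × √186 = 6.1 standard errors. Power is therefore about 100% for each instrument, which the simulation also showed.

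**The case against.** A reader might infer that the model cannot give the change on any outcome. The document does not support that. The time-by-assessment cell means are the mean of each instrument at each visit, and simple contrasts among them give each outcome's change. The same paragraph separately plans summary estimates at baseline and follow-up, and Cohen's d. The inputs for the later trial are not lost.

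A reader might also infer that scoring alone forces a significant interaction, or that a benefit cancelled in the time effect would go unseen. Neither follows. With no change on any scale, simulation under similar assumptions (n = 169, SDs 5, 4.5, 8 and 6) rejected the interaction in only about 6 to 8% of runs. With improvement on every scale the interaction was rejected in 100%, even where the time effect had no power, and simple effects are the usual next step. What remains is that a significant interaction does not say which outcome moved or whether it improved.

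The power figures rest on assumed SDs and also shift with the assumed correlation between instruments, so they show a mechanism and do not forecast this study. The sample size section says hypothesis testing of clinical outcomes is not central, and no decision rule hangs on the omnibus tests. Recruitment, retention and acceptability are untouched. This lowers the severity. It does not make the pooled tests interpretable, and it does not reconcile four with five.

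**Conclusion.** The point holds and is a should-fix. The stated 4 × 4 is wrong against the article's own list and Table 1. As specified, the omnibus tests neither estimate nor test change on any single outcome, which is what the paragraph's stated purpose requires.

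The opposite-direction argument rests on the symptom scales against the positive wellbeing scale, which the document does support. It does not depend on the direction of the functioning item or the range of the self-efficacy scale, neither of which is given. The structural conclusion needs no assumed SD. The size of the effect does, so the range of about 4% to 79% is illustrative only.

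**What to change.** Replace the single ANOVA with a separate repeated measures analysis for each of the five instruments, with time as a four-level factor. A linear mixed model is a suitable choice because it also uses records with a missed visit. A classical two-factor ANOVA needs all 5 × 4 = 20 scores from each participant, so one missing form removes that person from every outcome. Five separate repeated measures ANOVAs would also cure the pooling.

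For each instrument, report the change from T0 to T1, T2 and T3 with 95% CI, the SD at each visit, the correlation between baseline and follow-up, and Cohen's d. Delete 4 × 4 and the count of four assessments. While the paragraph is open, use one name for the functioning item, which is a 5-point Likert item in one section and a VAS in others.

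The cost is one rewritten paragraph and five routine models instead of one, with no new data.

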## Discussion

This study protocol is designed to test the feasibility, acceptability, and potential effects of a new online multimedia intervention, MePlusMe, which addresses mild to moderate psychological difficulties, as well as study skill difficulties experienced by HE students. The novelty of the system warrants an initial study to provide feasibility data. These data will provide valuable information regarding feasibility of recruitment strategies (including sample size) and the proposed outcome measures, alongside the extent of change between pre- and post- intervention ratings (mood, wellbeing, academic self-efficacy, and everyday functioning) and acceptability of the intervention, informing the implementation of future randomised trials assessing effectiveness.

MePlusMe provides students with an immediate personalised resource for support, which they are able to access in privacy from wherever they are, as often as they want, and at any time. In this way, they can preserve anonymity whilst developing their personal effectiveness and coping skills. The system offers a holistic and inclusive service by reaching out to the majority of students, even those who would not normally present to SSS for their difficulties. In addition, the system is designed in such a way that it can address a variety of needs as they change over time, and provides instant, tailor-made support. A multimedia format of the provided support renders the experience easy, fun, and thus more accessible and user-friendly. The system reinforces and empowers students to take responsibility for their wellbeing, and this in itself strengthens their self-efficacy and self-esteem.

In addition to the support that the students can enjoy by using the system, HEIs can also benefit from introducing MePlusMe to their students. It can represent a complementary, high-quality service alongside their existing support mechanisms. For example, personal tutors, untrained in counselling, may use the system as a first option for students experiencing difficulties. Moreover, counsellors can refer students with milder difficulties to the system, allowing them to concentrate on those especially in need of professional support. As such, MePlusMe can act as a filtering portal for the HEI SSS, and assist them to optimise their resources, whilst minimising their running costs. MePlusMe can further be used by students who are on a waiting list to receive support from SSS, ensuring that the students have some form of support in the meantime. After completing their sessions at the SSS (usually four or five sessions per student), the students can use MePlusMe as a complementary back-up support system. Whilst it can complement current services, the system can also act as a stand-alone resource, thus enriching HEIs offerings to their students. Α current limitation of MePlusMe is that the benefits of face-to-face psychological and study skill support cannot be provided. Future versions of the system are likely to include more direct modes of support by specialised professionals, either through emails, video-conferencing, or via offline face-to-face treatment.

The system is designed in such a way that it ensures that HEIs can attract and support students from different ethnic backgrounds, and help them fulfil their obligations to international students. The user data analytics provided by MePlusMe can offer HEIs access to their students’ mental health and academic needs, which can further assist them to identify how existing services can be resourced to reach higher efficiency. Therefore, MePlusMe can be part of the restructuring agenda for HEIs SSS, assisting them to promote themselves as a ‘caring university’, more effectively meet their pastoral role, increase course completion rates, reduce financial losses from drop-outs, optimise their resources, enhance students’ experience and satisfaction, improve their rankings, and increase their annual intake of students. This will aid their accountability to stakeholders on resources spent, and assist them to retain their funding and remain financially positive.

Overall, MePlusMe addresses common challenges faced by students by offering pragmatic coping mechanisms that de-stigmatise difficulties. Informed by current evidence-based psychological practice, it emphasises prevention rather than treatment. In addition, it represents a holistic solution for student support, which could minimise costs, while potentially offering a high-quality service. It is designed to reach out to the majority of students who do not require formal services, but still have difficulties that need to be addressed. In the current version, the psychological problem types addressed are anxiety symptoms, depression symptoms, and mixed anxiety and depression symptoms. Yet, the questionnaire used is designed in such a way that it is expandable. Thus, by adding more questions, it could further discriminate specific anxiety features. In future versions, features of conditions, such as social anxiety and seasonal affective disorder (SAD), will be considered for inclusion. Accordingly, new and appropriate techniques will be included to address these newly introduced conditions.

